#### Interim analyses {21b}

An interim analysis will be performed when 50% of the patients have been randomized and completed the 4 weeks follow-up period. This analysis will be performed to assess how many patients complete the primary outcome measurement and to estimate the drop-out rate. If the drop-out rate is higher than expected (i.e., > 10%), we should consider to update the sample size to prevent an underpowered study [29].

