### Trial design {8}

The BLEND RCT is a phase III randomized controlled trial within the PRospective Evaluation of interventional StudiEs on boNe meTastases (PRESENT) cohort including patients referred to the radiotherapy or orthopedic surgery department of the University Medical Center (UMC) Utrecht for the treatment of bone metastases, according to the Trials within Cohorts (TwiCs) design [1, 10]. At cohort enrolment, patients are asked consent for collection of demographic and clinical data, and patient-reported outcomes, and for randomization into future intervention studies [11]. Patients are informed that they will be randomized to either the intervention or control arm when meeting the inclusion and exclusion criteria of a future trial. When allocated to the intervention arm, they will be offered the intervention which they can accept or refuse. Informed consent is obtained from those patients accepting the intervention. When allocated to the control arm, patients will not be notified about the trial and their cohort data will be used comparatively. Patients who meet the pre-specified in- and exclusion criteria for the BLEND RCT and who have provided informed consent for randomization into future trials will be randomly allocated 1:1 to the intervention or control arm. A flow chart of the study is presented in Fig. 1.

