#### Sample size {14}

Four weeks after the start of treatment, patients in the control group may just have received radiotherapy or still need to undergo radiotherapy. Therefore, we assume that they do not experience a pain response yet at that time point. From the PRESENT cohort, we know that patients who did not experience a pain response after radiotherapy had a physical functioning mean score of 43.6, 4 weeks after the start of radiotherapy.

A recent study reported a minimal clinically important difference (MCID) of 13 points on the EORTC QLQ-C15-PAL physical functioning scale in patients with bone metastases undergoing radiotherapy [22]. To detect a 13 point difference with an 80% power, a two-sided *α* of 5% and standard deviation of 22, 45 patients are needed in each arm. We expect that 90% of the patients offered the intervention will accept the offer. To compensate for refusal, questionnaire nonresponse, and possible dropouts, we will increase the sample size by 10%, resulting in a total sample size of 100 patients.

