#### Methods in analysis to handle protocol non-adherence and any statistical methods to handle missing data {20c}

Analysis will be based on the intention-to-treat principle. However, in accordance with the TwiCs design, patients who are selected for the intervention arm may refuse the intervention. In case of a high refusal rate (i.e., > 15%), we will also conduct a per protocol (PP) analysis including patients who completed the treatment as allocated. However, refusal may be selective, e.g., patients who are less physically fit may refuse the intervention. As a result, PP analysis may under- or overestimate the treatment effect. We will also perform a complier average causal effect (CACE) analysis to estimate the treatment effect among “compliers,” i.e., patients that accepted and received the intervention offered compared with hypothetical control patients who, if offered the intervention, would have accepted.

In the palliative oncology setting, questionnaire non-response is more likely due to inability to complete questionnaires as a result of for example fatigue and high distress or filling in questionnaires may be too burdensome. The proportion and patterns of missing data for the primary and secondary outcomes will be investigated. If needed, multiple imputation methods will be used to handle missing data under the assumption that data is missing at random. If the primary outcome data is determined to be missing not at random, a best–worst and worst-best case sensitivity analyses will be performed.

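### The interim check against an underpowered trial looks only at drop-out; refusal of the offer, which dilutes the intention-to-treat effect, is not assessed

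*Protocol article*

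**What the plan says.** Interim analyses {21b} places one look after half the patients have been randomised and followed for four weeks. Its scope is given as: "This analysis will be performed to assess how many patients complete the primary outcome measurement and to estimate the drop-out rate". The only condition attached to it is: "If the drop-out rate is higher than expected (i.e., > 10%), we should consider to update the sample size to prevent an underpowered study".

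Sample size {14} expects some refusal: "We expect that 90% of the patients offered the intervention will accept the offer". It then names refusal, questionnaire non-response and drop-out as three separate items and covers all of them with a single 10% increase, from 45 to 50 per arm.

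Intervention description {11a} gives refusers the same standard of care as the control arm. The section on non-adherence and missing data {20c} makes intention to treat the basis of analysis. It sets the only threshold tied to refusal: "In case of a high refusal rate (i.e., > 15%), we will also conduct a per protocol (PP) analysis". A CACE analysis is also planned. Neither is linked to the sample size.

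**The concern.** Two things can erode power here. Missing 4-week questionnaires reduce the number of evaluable patients. Refusal leaves that number intact but shrinks the expected difference between arms, because some of the intervention arm received control treatment. The required sample size grows as 1/(1 - drop-out) for the first and as 1/(1 - refusal)² for the second, so a given percentage of refusal costs more than the same percentage of drop-out.

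The interim rule exists to protect power, yet it reads only the first quantity. Refusal is a built-in feature of the design and is known for every patient who has been offered the intervention. A trial could pass its interim check with complete questionnaires and substantial refusal, and end with a primary comparison weaker than its stated 80%. A null intention-to-treat result would then be hard to tell apart from low uptake that was already visible at the halfway point.

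**Working it through.** **Inputs.** From Sample size {14}: "To detect a 13 point difference with an 80% power", two-sided 5%, and "standard deviation of 22, 45 patients are needed in each arm". Total 100, so 50 per arm under 1:1 allocation. Expected refusal 10% (same section). High-refusal threshold 15% (section {20c}). Assumptions not in the protocol: the full 13 points in acceptors, no gain in refusers, SD 22 in both arms.

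**Reproducing the plan.** n per arm = 2 × (1.960 + 0.842)² × 22² / 13² = 44.96, so 45. Then 45 / 0.90 = 50 per arm, 100 in total. The stated figures reproduce. With the t-distribution, power at 45 per arm is 79.2%; with all 50 per arm evaluable it is 83.3%.

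**Adding refusal.** With refusal r, the intention-to-treat difference is 13 × (1 - r): 11.70 points at 10% and 11.05 at 15%. The standard error is 22 × √(2/n): 4.638 at n = 45 and 4.400 at n = 50. Power comes from the noncentral t with 2n - 2 degrees of freedom and noncentrality equal to difference / standard error. The rule is silent in both columns, since drop-out is exactly 10% in the first and zero in the second.

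| Refusal | Difference | Noncentrality, 45 / 50 | Power, 45 per arm | Power, 50 per arm |
|---|---|---|---|---|
| 0% | 13.00 | 2.803 / 2.955 | 79.2% | 83.3% |
| 10% (expected) | 11.70 | 2.523 / 2.659 | 70.4% | 75.0% |
| 15% (protocol's threshold) | 11.05 | 2.382 / 2.511 | 65.4% | 70.1% |
| 20% (illustrative only) | 10.40 | 2.242 / 2.364 | 60.2% | 64.8% |

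The normal approximation gives values about one point higher. Allowing for the extra variance from mixing acceptors and refusers lowers power by about one point.

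**What the trigger sees.** Drop-out of 20% with no refusal leaves 40 per arm and 74% power; the rule fires. Refusal of 15% with no drop-out leaves 70%; the rule does not fire. The weaker of the two trials passes.

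**Evaluable patients per arm for 80% power (normal approximation).** 45 / 0.90² = 55.6, so 56 at 10% refusal; 45 / 0.85² = 62.3, so 63 at 15%.

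**Covariate adjustment.** The primary analysis adjusts for baseline physical functioning and other covariates. If the baseline-outcome correlation is ρ, the residual SD is 22 × √(1 - ρ²): 20.99 at ρ = 0.3 and 19.05 at ρ = 0.5. The protocol gives no ρ, so both are assumptions. Power at 45 to 50 evaluable per arm:

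| Refusal | ρ = 0.3 | ρ = 0.5 |
|---|---|---|
| 10% | 74-79% | 82-86% |
| 15% | 70-74% | 78-82% |

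**The case against.** **Drop-out may be meant to include refusal.** The 10% in the interim rule matches the pooled 10% increase in Sample size {14}, which covers refusal as well. The reading is possible, but it is not what the text says. The sample size section lists refusal apart from drop-out, and section {20c} gives refusal its own threshold of 15%. If the pooled meaning was intended, the rule needs to say so.

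**The power figures are for an unadjusted test.** This stands in part. The planned analysis is linear regression or ANCOVA, and a baseline correlation of 0.5 would bring power at 15% refusal to about 80%. The protocol's own calculation takes no credit for adjustment, and a weaker correlation leaves a shortfall. A reader might infer that power is bound to fall far below 80%; the documents do not establish that at the refusal rate they expect, and rates of 20% or more appear nowhere in them.

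**Some refusers will also fail to return the questionnaire.** Section {20c} suggests refusers may be less fit and links non-response to inability to complete. So refusal is not wholly invisible to a drop-out count. Telephone follow-up for the primary outcome limits how much of it would show up that way.

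**The root lies in the sample size section.** Treating refusal as lost patients rather than as dilution does begin there. The interim rule is nevertheless a separate safeguard with its own stated purpose, and it could catch the problem while recruitment is still open.

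**The CACE analysis deals with non-uptake.** It helps interpret a null result. It does not restore power for the primary comparison or prompt a review of sample size.

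**A condensed article may omit further criteria.** The rule is stated here with its inputs, threshold and purpose. The point is that those inputs do not serve that purpose, not that detail is absent.

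**Conclusion.** The point holds. The interim rule, as written, guards against loss of data but not against dilution by refusal, and refusal is the more costly of the two per percentage point. With the rule silent, unadjusted intention-to-treat power is 70-75% at the expected 10% refusal and 65-70% at 15%, for 45 to 50 evaluable per arm. These figures rest on a 13-point effect in acceptors, none in refusers and SD 22. Adjustment could bring power at 15% refusal to about 70-74% or 78-82% under assumed correlations of 0.3 or 0.5, so the size of the shortfall is uncertain while the blind spot is not.

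It would go too far to infer that the sample size arithmetic is wrong, since it reproduces, or that the rule forbids a review prompted by refusal. It only says a change should be considered when drop-out exceeds 10%, and it is silent on refusal. This is worth correcting while recruitment is open.

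**What to change.** In Interim analyses {21b}, keep the drop-out count and add acceptance in the intervention arm. Project intention-to-treat power from both, using a difference of 13 × (1 - observed refusal) and evaluable n per arm of 50 × (1 - observed non-completion). Define drop-out, and say whether refusal counts towards it.

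A flat 80% trigger would not work: the plan's own expectations give 75.0% (10% refusal, no drop-out) or 70.4% (10% refusal, 10% drop-out), so it would fire with the trial on plan. Instead, state a planning scenario that already includes 10% refusal and add a review when observed refusal and non-completion together are worse than it. If the reference were 10% refusal with 10% non-completion (70.4%), then 15% refusal would call for a review with 10% non-completion (65.4%) and, narrowly, with none (70.1%). If covariate adjustment is to be credited, name the assumed correlation. If the sample size is not changed, restate the projected power.

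The wording change is short. Acceptance is already known for each patient offered the intervention, and no outcome data by arm are used, so the type I error is unaffected. The costs are more frequent reviews and a less favourable stated power. An increase may also be hard to achieve in a single centre. About 25 patients will be in the intervention arm at the look, so 10% and 15% refusal differ by little more than one patient (2.5 against 3.75). The projection should therefore be reported with its uncertainty.

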#### Methods for additional analyses (e.g., subgroup analyses) {20b}

Not applicable. There will be no additional analyses (e.g., subgroup and adjusted analyses).

#### Methods in analysis to handle protocol non-adherence and any statistical methods to handle missing data {20c}

Analysis will be based on the intention-to-treat principle. However, in accordance with the TwiCs design, patients who are selected for the intervention arm may refuse the intervention. In case of a high refusal rate (i.e., > 15%), we will also conduct a per protocol (PP) analysis including patients who completed the treatment as allocated. However, refusal may be selective, e.g., patients who are less physically fit may refuse the intervention. As a result, PP analysis may under- or overestimate the treatment effect. We will also perform a complier average causal effect (CACE) analysis to estimate the treatment effect among “compliers,” i.e., patients that accepted and received the intervention offered compared with hypothetical control patients who, if offered the intervention, would have accepted.

In the palliative oncology setting, questionnaire non-response is more likely due to inability to complete questionnaires as a result of for example fatigue and high distress or filling in questionnaires may be too burdensome. The proportion and patterns of missing data for the primary and secondary outcomes will be investigated. If needed, multiple imputation methods will be used to handle missing data under the assumption that data is missing at random. If the primary outcome data is determined to be missing not at random, a best–worst and worst-best case sensitivity analyses will be performed.

#### Plans to give access to the full protocol, participant-level data, and statistical code {31c}

Following publication of the study results, datasets containing de-identified patient-level data will be made accessible upon reasonable request to the principle investigator or the corresponding author. Data will be accessible in a digital workspace on a cloud-based platform.

### Oversight and monitoring

#### Composition of the coordinating center and trial steering committee {5d}

The principle investigator, coordinating investigators, spine surgeon, and radiation oncologist are responsible for the monitoring of study process. The project group will meet every 2 weeks to discuss the progress of the trial. Ad hoc meetings will be scheduled to address time-sensitive issues as they arise.

#### Composition of the data monitoring committee, its role and reporting structure {21a}

Data monitoring will be performed by an independent monitor who will monitor the progression of the study, check the presence of informed consent, review the presence of standard operating procedures (SOPs) and adherence to the study protocol, SOPs and the Medical Research Involving Human Subjects Act (WMO), and verify accuracy and completeness of the data. The monitor will brief any issues to the study team, who will address and resolve these issues and report back to the monitor.

#### Adverse event reporting and harms {22}

Adverse events during hospital stay will be evaluated using the most recent version of the CTCAE (version 5.0, version 6.0 when available at the start of the study). Due to the natural course of the disease, we expect that many patients with spinal metastases suffer from study unrelated AEs. Therefore, only study-related AEs with grade 2 or higher (either expected or unexpected) reported spontaneously by the patient or observed by the research team will be recorded up to three months after treatment.

Grade 3 or higher adverse events are considered serious (S) AEs. (S)AEs that are common in this patient category include urinary tract infections, delirium, pressure sores, and opioid-related adverse drug events and will be recorded but not reported to the ethics committee. Study-related SAEs within 3 months after start of treatment that are life threatening or that resulted in death will be directly reported (within 7 days) to the ethics committee. Other study-related SAEs will be reported to the ethics committee within 15 days. SAEs unrelated to the study will not be directly reported to the ethics committee but documented in the yearly progress report.

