Pain response at 2, 4, 6, and 8 weeks and 3 months is defined as [1] a decline in worst pain score of at least two points on an NRS of ten at the treated site without increase in analgesic use or [2] an analgesic decrease of at least 25% without an increase in pain score [25–27]. Worst pain score will be measured with the BPI [15, 16].

Information on duration of the hospital stay in days, days until return to systemic oncological therapy, local control, and progression free survival and overall survival will be captured from the electronic health record. Also, occurrence of neurological deterioration, defined as deterioration of more than one grade on the American Spinal Cord Injury Association (ASIA) scale as measured by physical examination by a neurologists or trained ASIA physician, will be captured from the electronic health record [19, 20].

AEs are defined as any undesirable experience occurring to a patient during the study that may be related to the experimental treatment procedure. AEs during hospital stay will be evaluated using the most recent version of the National Cancer Institute Common Toxicity Criteria of Adverse Events (CTCAE; version 5.0, version 6.0 when available at the start of the study). AEs after hospital discharge reported spontaneously by the patient or observed by the research team will be recorded up to 3 months after treatment.

For cost-effectiveness evaluation, resource use, costs, and quality-adjusted life years (QALYs) are measured for each patient in both randomization groups over the follow-up period. Resource use such as doctor visits, medication, hospital admissions, and surgical interventions, as well as out-of-pocket expenses such as for over-the-counter drugs and travel costs, will be captured using the iMCQ at 3 and 6 months [21]. Where relevant, questionnaire responses will be verified or completed by data from the medical records. Total costs for each patient will be calculated by multiplying the resource use with unit costs. Unit costs will be calculated according to the guidelines for costing research. QALYs will be calculated from the EQ-5D-5L, using the area under the curve approach [23].

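### Seriousness of an adverse event is set by CTCAE grade alone, so SAE status and expedited reporting do not follow the event's consequence

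*Protocol article*

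**What the plan says.** The rule is in the protocol article, section Adverse event reporting and harms {22}: "Grade 3 or higher adverse events are considered serious (S) AEs". The same section gives the source of the grade: "Adverse events during hospital stay will be evaluated using the most recent version of the CTCAE". It limits recording, up to three months after treatment, to "only study-related AEs with grade 2 or higher (either expected or unexpected").

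SAE status then governs reporting. Study-related SAEs "that are life threatening or that resulted in death will be directly reported (within 7 days) to the ethics committee". For the rest, "Other study-related SAEs will be reported to the ethics committee within 15 days". Two groups are kept out of these reports: a list of events common in this population (urinary tract infection, delirium, pressure sores and opioid-related events are named), and SAEs unrelated to the study, which go into the annual progress report.

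The section on assessment and collection of outcomes {18a} defines the AE itself without any element of seriousness: "AEs are defined as any undesirable experience occurring to a patient during the study that may be related to the experimental treatment procedure".

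**The concern.** Severity and seriousness are different properties. A grade describes how intense an event is. Seriousness, as a trigger for expedited reporting, should describe what the event led to. The section recognises this distinction in part, because it uses threat to life and death to pick out the fastest report. But it applies those two consequences only to events that have already qualified by grade.

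Classification can therefore go wrong in both directions. An event of moderate grade with an important consequence is left out of the SAEs, and an event of higher grade with no such consequence is included. The SAE count then measures severity under another name, and the ethics committee's expedited reports follow the grade.

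This matters more than usual here. The trial hypothesises no increase in wound complications despite the short interval between radiotherapy and surgery (Objectives {7}). It cites mixed evidence on preoperative radiotherapy (Discussion), and its earlier experience with the procedure is 13 patients (Provisions for post-trial care {30}). The independent monitor's listed tasks concern consent, procedures, adherence and data accuracy {21a}, and the interim analysis concerns completion and drop-out {21b}. Reporting to the ethics committee is thus the only expedited external route for individual events that the article describes, and the grade rule is the gate to it.

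**Working it through.** The article gives no event rate and no figure to reproduce, so the check consists of reading the rules together and applying them to cases.

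**Step 1: is there any other definition of seriousness?** The places that could hold one are the outcome list {12}, the assessment section {18a}, the section on post-trial care {30}, the monitoring section {21a} and the harms section {22}. Only the harms section defines an SAE, and it does so by grade. Admission, longer stay, readmission and lasting disability are not named anywhere as criteria. Threat to life and death appear only to choose between the two reporting deadlines.

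**Step 2: apply the rules as written to study-related events.**

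| Study-related event | Recorded | SAE | Report to ethics committee |
|---|---|---|---|
| Grade 2, lengthens admission or causes readmission | yes | no | none stated |
| Grade 3, no serious consequence, not a listed common event | yes | yes | within 15 days |
| Grade 3, listed common event | yes | yes | exempt |
| Grade 3 or higher, life threatening or fatal | yes | yes | within 7 days |

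The first two rows show the mismatch: the event with the consequence has no report, and the event without it has one. The third row shows that the over-inclusion is limited by the section's own exemption.

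**Step 3: is the grade itself fixed for the events concerned?** CTCAE evaluation is stated for events during the hospital stay. After discharge, the assessment section says: "AEs after hospital discharge reported spontaneously by the patient or observed by the research team will be recorded up to 3 months after treatment". No grading scale is named there, although the grade 2 threshold runs to three months. Readmission by definition follows discharge, so for such an event SAE status depends on a grade whose basis the article leaves unclear. Clinicians and researchers are also aware of allocation {17a}, so the judgement between grade 2 and grade 3 is an unblinded one.

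**Step 4: what is still captured?** "Information on duration of the hospital stay in days" is among the items taken from the electronic health record {18a}. Hospital admissions are collected in both groups with the iMCQ at 3 and 6 months and, where relevant, checked against medical records {18a}. Study-related grade 2 events are recorded {22}. The information needed to judge consequence is therefore largely collected, but it is not connected to the SAE definition.

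**The case against.** Four points can be made on the other side.

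First, the sentence does not say that grade is the only criterion, and the article condenses a full protocol that may contain others. This stands as a limit: the grade 2 half of the point is inferred from the absence of any other route. But the article states a rule here and does not merely omit one. If the full protocol has consequence-based criteria, the sentence is at odds with them and the two must be reconciled.

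Second, the CTCAE grade definitions are not reproduced. If they already take account of admission or disability, some events that lengthen the stay would be graded 3 or higher in any case. This also stands. It could shrink the grade 2 gap by an amount the article does not let one determine. It would leave the grade 3 event without serious consequence classed as an SAE.

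Third, over-reporting of grade 3 events is conservative and is limited to study-related events outside the exempt list. This is correct, and that half of the point is the less important one.

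Fourth, no data are lost, because recorded AEs, length of stay and admissions remain available. This is correct and sets the scope. A reader might infer that the rule conceals the wound events most informative for safety, or leaves the trial unable to answer its wound-complication question. The article does not support that: a study-related grade 2 wound event is still recorded and can be analysed without the SAE label. What it lacks is a stated expedited report.

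**Conclusion.** The point holds as one about classification and reporting. Grade 3 or higher is the only stated criterion for seriousness. A study-related grade 2 event with prolonged admission or readmission therefore has no stated route to an expedited report, while a non-exempt study-related grade 3 event without serious consequence has one.

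The size cannot be given as a number. The article provides neither the frequency of events that lengthen the stay nor the share that would be graded 2. Its only wound figure is none among 13 patients in the first-in-man study. Any count of affected events would rest wholly on assumed rates.

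The conclusion assumes that the article's rule is the one applied in the trial and that some events with these consequences can be graded 2. The sample size, the primary analysis and the capture of study-related AEs of grade 2 or higher are untouched. The change is worth making because it is cheap and improves what SAE counts and expedited reports mean.

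**What to change.** In the harms section {22}, replace the grade rule with a definition by consequence: death, threat to life, admission or prolonged admission, or persistent disability, whatever the CTCAE grade. Say that admission means admission caused by the event, since every patient is admitted for the planned treatment. Record the CTCAE grade separately as severity, and state that it also applies to events after discharge. The existing 7-day and 15-day deadlines and the exemption list can stay, provided they refer to the new definition.

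The cost is a change of wording, submitted as an amendment if judged substantial {25}, and one extra field on the adverse event form. The number of reported SAEs may shift slightly in either direction. Where patients have already been recruited, recorded events should be reclassified under the new definition so that SAE counts are consistent over the whole trial.

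### The serious adverse event rules overlap with no stated precedence, and recording only study-related events does not match the yearly report or the comparison between arms

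*Protocol article*

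**What the plan says.** All the reporting rules stand in Adverse event reporting and harms {22}:

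- **Seriousness.** It is set by grade alone: "Grade 3 or higher adverse events are considered serious (S) AEs".
- **Recording.** Because many unrelated events are expected in this disease, the section records "only study-related AEs with grade 2 or higher (either expected or unexpected"), up to three months after treatment.
- **Common events.** (S)AEs usual in these patients are introduced by the word 'include', with four examples (urinary tract infection, delirium, pressure sores, opioid events). The sentence ends "opioid-related adverse drug events and will be recorded but not reported to the ethics committee".
- **Study-related SAEs, most severe.** Those within 3 months of starting treatment "that are life threatening or that resulted in death will be directly reported (within 7 days) to the ethics committee".
- **Study-related SAEs, remainder.** "Other study-related SAEs will be reported to the ethics committee within 15 days".
- **Unrelated SAEs.** "SAEs unrelated to the study will not be directly reported to the ethics committee but documented in the yearly progress report".

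Outcomes {12} and Plans for assessment and collection of outcomes {18a} define an adverse event as "any undesirable experience occurring to a patient during the study that may be related to the experimental treatment procedure". Section {18a} adds that "AEs after hospital discharge reported spontaneously by the patient or observed by the research team will be recorded up to 3 months after treatment". Objectives {7} lists adverse events, wound complications among them, as a secondary comparison between the two arms.

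**The concern.** Two things do not fit together.

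First, the common-event sentence and the 7- and 15-day sentences apply to overlapping sets of events and give different instructions. Nothing says which yields. Since the list is open, the team can also extend the set of events to which the exemption might apply.

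Second, relatedness decides whether an event is recorded at all, yet events judged unrelated are owed to the ethics committee once a year. The same filter sits upstream of a comparison between arms. Who will be blinded {17a} says that researchers and clinicians cannot be blinded to allocation, so any attribution they make is made with the arm known.

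The ethics committee is the only body outside the study team that the article names as receiving SAE reports. The monitor in section {21a} checks consent, procedures, adherence and data quality; no safety-review role is described. The safety experience cited for same-day treatment is one study of 13 patients (Provisions for post-trial care {30}; Discussion), so the harms data from this trial will carry weight.

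**Working it through.** No arithmetic applies, and the article states no figure to reproduce. The check takes each class of SAE (grade 3 or higher) and reads off every sentence that applies to it.

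| Class of SAE | Recorded? | Sent to the ethics committee? | Consistent? |
|---|---|---|---|
| 1. Listed as common, study-related, life threatening or fatal | Yes | Not reported (common-event rule); within 7 days (related-SAE rule) | No |
| 2. Listed as common, study-related, other | Yes | Not reported; within 15 days | No |
| 3. Listed as common, unrelated | Yes (common-event rule); no (recording rule) | Not reported; in the yearly report | No |
| 4. Not listed, unrelated | No (recording rule and adverse event definition) | In the yearly report | No |
| 5. Not listed, study-related | Yes | Within 7 or 15 days | Yes |

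Four of the five classes carry a conflict. If rows 1 and 2 are merged, it is three of four.

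**Rows 1 and 2.** The common-event sentence has no qualifier for relatedness or outcome. The 7- and 15-day sentences have no exception for listed events. A grade 4 delirium judged study-related is therefore both exempt and, if life threatening, due within 7 days. A grade 3 delirium judged study-related is both exempt and due within 15 days. Being an expected event does not take it out of the related class, because the recording rule covers expected and unexpected related events alike.

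**Rows 3 and 4.** SAEs start at grade 3, so they lie inside the recording rule that starts at grade 2, and that rule admits related events only. The definition in {12} and {18a} narrows this further to events possibly related to the experimental procedure. The yearly report must nevertheless cover unrelated SAEs. The article names no trial record that would hold them.

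**Comparison between arms.** The adverse event count in each arm is a count of events that passed the relatedness filter. If attribution differs by arm, the comparison differs with it, and events filtered out leave no entry from which attribution could be re-examined. The definition refers to the experimental procedure, which control patients are not planned to receive; the article does not say how a control-arm event is to be judged against it.

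**The case against.** The best defence is that the section can be read in order. It opens with background events due to the disease, the common-event sentence continues that theme, and the rules for study-related SAEs then follow as the specific case. On that reading a related event always goes to the committee. This is plausible and may be what was meant, but the precedence is not written.

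A second defence is that the recording limit may govern only the period after discharge. Its wording resembles the post-discharge sentence in {18a}, and in-hospital events have their own grading sentence. This is possible but also not written. Even so, unrelated SAEs after discharge would go unrecorded, and the definition would still turn on possible relatedness.

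Third, the data are not lost altogether. Overall survival and neurological deterioration come from the health record whatever the cause, so a death called unrelated stays in the trial data. The monitor also verifies accuracy and completeness. Both points stand and limit the consequence. Neither supplies a record of unrelated SAEs for the yearly report.

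Fourth, the article condenses an approved protocol (version 02, Trial status) that is not shown. That would excuse missing detail. Here the stated sentences disagree with one another; if the full protocol settles it, the article only needs to be brought into line.

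A reader might infer that listed events are never reported, even when study-related or fatal. The documents do not support this. The exemption is silent on relatedness and death, the next two sentences require related SAEs to be reported, and an unrelated fatal event falls under the yearly-report sentence. Nor can it be said that the exemption covers a large share of SAEs, since no frequencies are given.

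**Conclusion.** The concern holds as a conflict between stated rules. A listed common event judged study-related falls under two incompatible instructions with no precedence, so it may go unreported. Separately, the recording rule excludes the unrelated SAEs that the yearly report requires, and it makes the comparison of adverse events between arms depend on attribution by unblinded staff.

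The size is four of five event classes in conflict. The number of patients or events affected cannot be derived from the article. Sample size, power, type I error and the primary outcome are untouched. What is exposed is safety oversight and one secondary comparison. The conclusion rests on reading the sentences as written; the softer readings would shrink the conflict, but the text does not choose them. This review does not say which reporting rule should prevail, only that the sentences must be reconciled.

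**What to change.** 1. In Adverse event reporting and harms {22}, state which rule takes precedence when a listed common event is judged study-related, for life-threatening or fatal events and for the rest.
2. Replace the open list by a closed one.
3. Record every grade 3 or higher event in both arms regardless of relatedness, with relatedness as a separate field, and align the definition in {12} and {18a}. The yearly report can then be compiled, and the arms can be compared on all such events as well as on those judged related.

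The cost is amendment wording and some additional SAE entries taken from the health record. Listing the exempted events by arm in the yearly report would go further, but that is a preference and is not needed to remove the conflict.
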